## Abstract

**Background:**

Sciatica is a common condition worldwide that is characterized by radiating leg pain and regularly caused by a herniated disc with nerve root compression. Sciatica patients with persisting leg pain after six to eight weeks were found to have similar clinical outcomes and associated costs after prolonged conservative treatment or surgery at one year follow-up. Guidelines recommend that the team of professionals involved in sciatica care and patients jointly decide about treatment options, so-called interprofessional shared decision making (SDM). However, there are strong indications that SDM for sciatica patients is not integrated in daily practice. We designed a study aiming to explore the barriers and facilitators associated with the everyday embedding of SDM for sciatica patients. All related relevant professionals and patients are involved to develop a tailored strategy to implement SDM for sciatica patients.

**Methods:**

The study consists of two phases: identification of barriers and facilitators and development of an implementation strategy. First, barriers and facilitators are explored using semi-structured interviews among eight professionals of each (para)medical discipline involved in sciatica care (general practitioners, physical therapists, neurologists, neurosurgeons, and orthopedic surgeons). In addition, three focus groups will be conducted among patients. Second, the identified barriers and facilitators will be ranked using a questionnaire among a representative Dutch sample of 200 GPs, 200 physical therapists, 200 neurologists, all 124 neurosurgeons, 200 orthopedic surgeons, and 100 patients. A tailored team-based implementation strategy will be developed based on the results of the first phase using the principles of intervention mapping and an expert panel.

**Discussion:**

Little is known about effective strategies to increase the uptake of SDM. Most implementation strategies only target a single discipline, whereas multiple disciplines are involved in SDM among sciatica patients. The results of this study can be used as an example for implementing SDM in other patient groups receiving multidisciplinary complex care (e.g., elderly) and can be generalized to other countries with similar context, thereby contributing to a worldwide increase of SDM in preference sensitive choices.

## Background

Sciatica, more accurately called lumbosacral radicular syndrome, is a form of radiating back pain, mostly caused by a herniated disc with nerve root compression. It is characterized by radiating leg pain in combination with dermatomal motor, sensory, or tendon reflex abnormalities. Sciatica is a common condition worldwide. In Western countries 5 to 10 per 1,000 persons annually develop sciatica, with variable pain intensities and disease course [1]. In the Netherlands, sciatica patients are initially diagnosed by general practitioners (GPs) and advised to continue daily activities with or without physical therapy (conservative treatment). After a period of six to eight weeks, the leg pain diminishes in 70 % of the patients [2]. The remainder of the patients is usually referred to a neurologist for further investigation, often involving an MRI. If the MRI confirms a herniated disc, compatible with the radicular symptoms, the patient can be referred to the neurosurgeon or orthopedic surgeon to consider surgery [3,4]. In general, surgery leads to more rapid relief than prolonged conservative treatment in patients suffering radiating leg pain for more than eight weeks, but with smaller risks for prolonged conservative treatment, and both treatments have similar outcomes and societal costs at one year follow-up [5-7]. Therefore, the Dutch multidisciplinary guideline recommends that the team of professionals involved in sciatica care and patients jointly decide about treatment after this six to eight week period, i.e., surgery or prolonged conservative treatment, based on the evidence regarding associated risks and benefits and preference of the patient [8]. After all, both treatment options have equivalent results and the choice thus can be considered preference sensitive. This situation is optimally suited for interprofessional shared decision making (SDM) [9].

SDM enables patients to make an informed choice in collaboration with the professionals involved, and is important for providing care consistent with patient preferences. The Dutch government tries to make healthcare more patient-orientated, for example, by enabling free choice of insurance company, and a law that obligates professionals to discuss consequences and risks of each treatment option [10]. Despite these efforts to deliver patient-centered care, and the sciatica guideline recommendation, there are strong indications that SDM for sciatica patients is not yet widely used. Recently, a comparison between regions in the Netherlands showed considerable variation in the number of patients that undergo surgery, ranging from 31 to 140 per 100,000 inhabitants [11]. In addition, Dutch surgery rates for sciatica patients are four times higher than those in the UK and two times higher than in Sweden [11]. Only the United States have a 40 % higher surgery rate than The Netherlands [12]. This is remarkable, because the guidelines in the United States and the UK show similarities, and both suggest referring patients to a specialist when they do not respond to standard noninvasive treatment or suffer from neurological deficits [13,14]. It is very unlikely that this (inter)national variation is only caused by case mix and patient preferences. Research has shown that patients prefer a shared approach over a physician-dominated one, and are more likely to favor conservative treatments over surgery after patients’ decision aid (DA) exposure [15,16]. Furthermore, it has been shown that Dutch patients are used to delegate treatment decisions to their professionals, so that professional preferences dominate treatment decisions [17]. Thus, it is far more likely that noncompliance with the evidence-based back pain guidelines, specifically the lack of applying SDM, combined with surgeon preferences are responsible for the varying surgery rates. SDM may diminish this variation, prevent underuse and overuse of surgery [18], and thereby improve quality of care.

### Objective

The DISC study (the Dutch Implementation Study of interprofessional Shared Decision Making in Sciatica) aims to explore the barriers and facilitators associated with the everyday embedding of SDM for sciatica patients in the Dutch healthcare context, among all involved professionals and patients, and to develop a tailored, team-based, strategy for SDM implementation among sciatica patients.

## Methods

The study consists of two phases (Table 1).

A. Identification of barriers and facilitators

i. Barriers and facilitators are explored for SDM implementation

**Table 1 T1:** Study phases and time schedule

	**Planning (months)**
**Phase A. Identification of barriers and facilitators**	
i. Barriers and facilitators are explored for SDM implementation	
Literature study and preparation interviews/focus groups	1 to 3
Interviews and focus groups	3 to 10
ii. Identified barriers and facilitators are ranked by importance in a representative sample	
Survey among professionals and patients	11 to 13
**Phase B. The development of an implementation strategy based on phase A**	
Development of the implementation strategy and expert panel	13 to 15
Writing report	16

### Study design

Barriers and facilitators among relevant stakeholders are explored in an interview study among professionals and in a focus group study among patients. The semi-structured interviews and focus groups are based on the framework developed by Grol and Wensing [19] in combination with the Normalization Process Model (NPM) [20]. The framework of Grol and Wensing [19] describes barriers and facilitators at the levels of the innovation, the professional, the patient, the social context, the organizational context, and the external environment (political and economic factors). However, the organizational context of their framework does not cover all relevant aspects for the implementation of SDM in practice. Therefore, we additionally use the NPM, which includes more details with respect to the organizational context [20] than the framework of Grol and Wensing. Normalization in the NPM is defined as the routine embedding of a complex intervention in healthcare, and this model thus offers a robust structure for investigating the collective work that leads to this embedding (or not), including:

1. Endogenous factors

a. Interactional workability: influence of SDM on interactions between people and practices.

b. Relational integration: relationship of SDM to existing knowledge and relationships.

2. Exogenous factors

a. Skill set workability: influence of SDM on current division of labor.

b. Contextual integration: relationship of SDM to the organizational setting.

The combination of the two frameworks thus ensures that all relevant aspects affecting implementation of SDM will be covered. The semi-structured interviews will be conducted among all professionals involved in the diagnosis and treatment of sciatica patients (GPs, physical therapists (PTs), neurologists, neurosurgeons, and orthopedic surgeons).

The focus group procedures of Morgan et al. will be used in preparing and conducting the focus group sessions [21]. A moderator and an observer will guide the focus groups. A group will consist of six to eight participants. When information saturation is not reached after this initial round, the focus groups will be extended in specific groups.

### Study population

We anticipate interviewing eight professionals in each of the target groups (GPs, PTs, neurologists, neurosurgeons, and orthopedic surgeons). In each group of professionals, we will continue until data saturation is reached, defined as three consecutive interviews without new ideas emerging (stopping criterion) [22]. To obtain contrasting views on barriers and facilitators, we select professionals from specific regions with either high surgery rates (most likely to raise barriers for SDM) or low surgery rates (most likely to raise facilitators for SDM) based on published reports [11,23]. In addition, we ensure diversity of gender and hospital type (public hospital and private treatment centers), because this may influence the experienced barriers and facilitators.

We anticipate organizing three focus groups, with six to eight patients in each group [24]. To create homogeneous groups, one focus group will include patients who have had surgery, one will include patients who have had conservative treatment, and one focus group will include patients that still have to decide on treatment. Patients will be recruited through advertisements in the local newspapers. When needed, additional patients will be recruited via the patient registries of GPs, neurologists, neurosurgeons, and orthopedic surgeons coordinated by the Spine Intervention Prognostic Study (SIPS) Group.

Inclusion criteria for patients are: age ≥18 years, a doctor’s diagnosis of sciatica no longer than 12 months ago, and a written informed consent. Patients with an inability to understand written and oral Dutch instructions or with active diseases likely to interfere with the purpose of this study, such as a terminal illness or severe psychiatric diseases, will be excluded from the study.

### Analysis

The semi-structured interviews and focus group interviews will be audio-taped and transcribed in full. They will be qualitatively analyzed using thematic framework analysis [25] to classify and organize data according to key themes, concepts and predefined categories. The predefined categories of the framework of Grol and Wensing will be used [19] regarding the level of the innovation, the professional, the patient, the social context, the organizational context, and the external environment (political and economic factors). We will compare the barriers and facilitators, to look for differences that may explain lack of SDM implementation. We use Atlas.ti software for analysis.

### Outcome measures

This study phase results in a list of identified barriers and facilitators for the implementation of SDM, grouped in a commonly used theoretical framework.

ii. Identified barriers and facilitators are ranked by importance in a representative sample

### Study design

We will conduct an internet-based questionnaire study among professionals and patients, to rank the identified barriers and facilitators from the interviews and focus groups. A maximum difference scaling (MaxDiff) exercise with an orthogonal design will be included in this questionnaire [26]. MaxDiff is a method to rank multiple items in a more efficient manner, with the additional advantage of scale-free rating so that it prevents scale use bias [27]. With this method, respondents choose the most and least important item within a set of items (Figure 1), with different sets offered to respondents a number of times.

**Figure 1 F1:**
[figure not shown]
Hypothetical example of MaxDiff task.

Each set thus provides more information than a number of pairwise comparisons and forces tradeoffs between items, thereby resulting in greater discrimination. A MaxDiff task is easy to complete for participants, and results in ratio-scaled scores of importance [26,28]. The order of items will be randomized between respondents, and each item will be equally represented, to avoid higher importance given to first mentioned items.

### Study population

The survey will be sent to a representative sample of GPs (n = 200), PTs (n = 200), neurologists (n = 200), all neurosurgeons (n = 124), orthopedic surgeons (n = 200) and patients (n = 100).

The sample of professionals will be randomly selected from the Dutch medical address book and the membership lists of the professional organizations. The neurosurgeons (n = 124) are included from the same sources. We will sample patients using the patient registries of GPs, PTs, neurologists, neurosurgeons, and orthopedic surgeons, and advertisements in local newspapers.

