### Analysis

Based on the choices made by respondents, importance scores will be estimated for each barrier and facilitator, for each individual respondent, using hierarchical Bayes estimation [29]. Differences between groups of respondents will be further analyzed in SPSS.

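### The survey's 100 patients are called representative, but unlike the professionals they come from an unspecified mix of registries and newspaper advertisements with no random draw stated

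*Protocol article*

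**What the plan says.** All references are to the protocol article.

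- **Abstract, Methods.** The ranking questionnaire is to be held among "a representative Dutch sample of 200 GPs, 200 physical therapists, 200 neurologists, all 124 neurosurgeons, 200 orthopedic surgeons, and 100 patients".
- **Phase A, step ii, Study population.** "The survey will be sent to a representative sample of GPs", and the same sentence runs on through the other professions to patients (n = 100). Table 1 and the heading of this step also use the word *representative*.
- **Same section, professionals.** "The sample of professionals will be randomly selected from the Dutch medical address book and the membership lists of the professional organizations". For the one profession taken whole: "The neurosurgeons (n = 124) are included from the same sources".
- **Same section, patients.** "We will sample patients using the patient registries of GPs, PTs, neurologists, neurosurgeons, and orthopedic surgeons, and advertisements in local newspapers".
- **Phase A, step ii, Analysis.** "Based on the choices made by respondents, importance scores will be estimated for each barrier and facilitator, for each individual respondent".
- **Discussion.** The authors name selection of patients and professionals as a possible limitation. For the survey they plan several reminders and a comparison of responders with non-responders on gender, hospital type and hospital location, in order to judge whether results carry over to the total sample.

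**The concern.** One adjective covers six groups that are selected in two different ways. A random draw from a list, or the whole list, makes the invited group representative of that list by design. A mix of clinic registries and people who answer a newspaper notice does not, unless something further is said about how the mix is formed, and nothing is.

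The article itself treats the uncontrolled factors as relevant. In Phase A, step i, it separates patient focus groups by treatment status (operated, conservatively treated, undecided), and it selects professionals from regions with high and low surgery rates because it expects them to raise different issues. The Background reports regional rates from 31 to 140 per 100,000, a ratio of 140/31 = 4.5. Local newspapers and an unspecified blend of registries leave both region and treatment history of the surveyed patients to chance.

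At stake is how the patient ranking may be described and used. The survey yields the list of the 10 most important barriers and facilitators, and Phase B builds the implementation strategy on that list.

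**Working it through.** The plan contains no power, precision or response calculation for the survey, so there is no figure of that kind to reproduce. The check is a count by selection method and a comparison of the sections.

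**1. Count by selection method** (group sizes from Phase A, step ii, Study population).

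| Group | n | Selection stated |
|---|---|---|
| GPs | 200 | random, from lists |
| Physical therapists | 200 | random, from lists |
| Neurologists | 200 | random, from lists |
| Orthopedic surgeons | 200 | random, from lists |
| Neurosurgeons | 124 | all, from the same lists |
| Patients | 100 | registries and advertisements, no random draw stated |

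Professionals: 4 × 200 + 124 = 924. Total: 924 + 100 = 1,024. Shares: 924/1,024 = 90.2% and 100/1,024 = 9.8%. The claim has a stated basis for the 90.2% and none for the 9.8%.

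**2. Does the planned non-response check fill the gap?** It needs people who were approached and did not answer. Someone who answers an advertisement belongs to no list of people approached, so there is no comparison group. Two of the three variables describe hospitals, and treatment history is not among them. The check also reaches only as far as the total sample; it cannot supply representativeness that was absent when the patients were selected.

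**3. Sent, ranked among, or recruited?** The Study population section gives numbers to whom the survey is sent, the Analysis section uses respondents, and the abstract gives the same numbers as the sample among whom ranking is done. These agree only at 100% response. The article gives no response rate, so the following is illustration under assumed rates (respondents = invited × rate).

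| Assumed response | Each group of 200 | Neurosurgeons (124) | Patients, if 100 means invited |
|---|---|---|---|
| 70% | 140 | 87 | 70 |
| 50% | 100 | 62 | 50 |
| 30% | 60 | 37 | 30 |

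The last column depends on a reading that the text does not settle. Advertisement recruits come forward by themselves and cannot be listed in advance as invitees, so 100 may mean patients recruited.

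**4. Precision of a split by recruitment source.** As a rough guide, the 95% half-width for a proportion of 0.5 is 1.96 × √(0.25/n). This gives 9.8 percentage points at n = 100, 13.9 at n = 50 and 17.9 at n = 30. MaxDiff scores are not simple proportions, so these figures show only that a ranking without the advertisement recruits would be descriptive.

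**The case against.** The strongest reply is that the authors have seen the problem. The Discussion names selection of patients as a limitation, plans reminders and treats generalizability as something to be tested. The Study population section says plainly that the survey is sent to these numbers, and the Analysis section says respondents, so the methods do not pass invitations off as completed questionnaires. No power or precision claim hangs on the figures, and an expected response rate is the kind of detail that an article may leave to a full protocol.

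Most of this stands. It rules out three stronger readings that a reader might infer:

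- *The whole survey sample is not representative.* The text does not support this: 924 of the 1,024 are a random draw or a full enumeration, and non-response among them is acknowledged and addressed.
- *The sample sizes are wrong.* They are not. The abstract condenses numbers sent into numbers ranked among, which is loose wording. Any shortfall depends on response rates that the article does not give.
- *The patient sample could consist entirely of volunteers.* Five types of registry are named ahead of advertisements and joined to them by *and*, so this is an extreme case and not the evident plan.

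Nor does the article show that advertisement recruits would rank items differently; that is plausible but unproven. What the reply does not answer is the patient group itself. A general limitation in the Discussion does not justify an unqualified claim in the abstract and methods, and the planned check does not reach advertisement recruits.

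**Conclusion.** The point holds for the patient group only. The article claims a representative sample of 100 patients without a selection method that could give one, and its planned check cannot make up for this among people recruited by advertisement. The affected part is 100 of 1,024 (9.8%), but it is the whole of the patients' voice in the ranking. The size and direction of any bias cannot be derived from the article, because neither the advertisement share nor its relation to the answers is given. The conclusion rests on the text as published. It would change if the full protocol specified a random draw from the registries and a minor or separately reported role for advertisements. The difference between numbers sent and numbers ranked among is a secondary matter of wording, apart from the real ambiguity about what n = 100 patients counts.

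**What to change.** 1. Restrict *representative* to the invited professional groups in the abstract, Table 1, the step heading and the Study population section. Describe the patients as recruited from registries and advertisements.
2. Record each patient's recruitment source and treatment history; the focus groups already separate patients by the latter. Report the patient ranking for all patients and again without those recruited by advertisement.
3. Where feasible, approach registry patients first and use advertisements as a back-up.
4. In the abstract, give the professional figures as numbers invited, as the Study population section already does, and state whether 100 patients means invited or recruited.

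The first and last changes are wording. The second adds two questionnaire items and one descriptive analysis, with the limited precision shown above. The third may mean somewhat more registry work. The price is a less favourable description of the patient sample. Random draws with fixed quotas across all five registry types would be stronger, but they are a larger change to recruitment and are not needed to resolve this point.

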### Analysis

Based on the choices made by respondents, importance scores will be estimated for each barrier and facilitator, for each individual respondent, using hierarchical Bayes estimation [29]. Differences between groups of respondents will be further analyzed in SPSS.

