### Outcome measures

A list of the 10 most important barriers and facilitators for implementation of SDM among sciatica patients.

B: Development of a tailored implementation strategy

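### Comparing exported hierarchical Bayes scores between respondent groups in SPSS would drop their posterior uncertainty; group differences should come from the upper level of the model

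*Protocol article*

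**What the plan says.** The point concerns Methods, phase A(ii), the internet survey with the MaxDiff exercise.

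- **Analysis, step one:** "importance scores will be estimated for each barrier and facilitator, for each individual respondent, using hierarchical Bayes estimation".
- **Analysis, step two:** "Differences between groups of respondents will be further analyzed in SPSS".
- **Study population:** the survey goes to 200 GPs, 200 physical therapists and 200 neurologists, and to "all neurosurgeons (n = 124), orthopedic surgeons (n = 200) and patients (n = 100").
- **Study design:** the size of the task is left open. Respondents choose within sets, "with different sets offered to respondents a number of times", and the number of items depends on the interviews and focus groups.
- **Outcome measures:** the one named result of this phase is "A list of the 10 most important barriers and facilitators for implementation of SDM among sciatica patients".

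The article does not say whether respondent group enters the upper level of the model. It does not name the test or interval to be used in SPSS, or say how the uncertainty of the individual scores is carried into that step.

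**The concern.** A hierarchical Bayes score for one respondent is not a measurement. It is a compromise between that person's few choices and the population distribution in the upper level, and it has a posterior spread. On the natural reading of the second step, SPSS receives one number per item per respondent, and the spread stays behind.

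What follows depends on the upper level. With one common mean, everyone is pulled toward a centre set mostly by professionals, and group differences shrink. With group-specific means, each respondent is pulled toward the right centre, but the scores within a group become too alike, and a standard error computed from their scatter is too small.

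The study wants a strategy tailored to a team of professions and to patients. It chose MaxDiff partly because the scores are ratio-scaled, so the size of a difference is meant to be read. If differences are understated, the groups look more alike than they are. If standard errors are too small, chance differences look real.

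**Working it through.** The article gives no power, effect size, SD or precision for this step, so there is no figure of its own to reproduce.

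**Inputs from the article.** Invited professionals: 200 + 200 + 200 + 124 + 200 = 924. Invited patients: 100. Total 1,024, so professionals are 924/1,024 = 90% of the pool.

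**Assumptions (not in the article).** All invited respond; 12 to 40 items; 10 to 24 sets of four; between-respondent SD τ of 1 or 2 logits.

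**1. Normal approximation.** Let τ² be the true variance between respondents within a group and s² the error variance of one respondent's score. The reliability is L = τ²/(τ² + s²). Set τ = 1 and take a true patient-professional difference d = 0.5. The unshrunken difference has

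SE = √[(1 + s²)(1/100 + 1/924)] = √[(1/L) × 0.01108].

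*Common mean.* Each score keeps a fraction L of its distance from the overall mean. The estimate is about L·d and the second-step SE is L·SE. The bias in SE units is (1 − L)d/(L·SE).

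*Group-specific means.* The estimate is unbiased for d, but the second-step SE is still L·SE. Coverage is 2Φ(1.96L) − 1, and the error rate of a nominal 5% test is one minus that.

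| L | SE | Common mean: estimate (true 0.50) | Common mean: second-step SE | Common mean: 95% coverage | Group means: 95% coverage | Group means: error rate of 5% test |
|---|---|---|---|---|---|---|
| 0.3 | 0.192 | 0.15 | 0.058 | 0.00 | 0.44 | 0.56 |
| 0.5 | 0.149 | 0.25 | 0.074 | 0.08 | 0.67 | 0.33 |
| 0.7 | 0.126 | 0.35 | 0.088 | 0.60 | 0.83 | 0.17 |
| 0.8 | 0.118 | 0.40 | 0.094 | 0.81 | 0.88 | 0.12 |
| 0.9 | 0.111 | 0.45 | 0.100 | 0.92 | 0.92 | 0.08 |

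Letting the pooled variance absorb the between-group difference changes the common-mean coverages only slightly, to 0.00, 0.09, 0.62, 0.82 and 0.92.

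Under a common mean the z statistic does not change. At L = 0.5 it is 0.50/0.149 = 3.36 before shrinkage and 0.25/0.0744 = 3.36 after. With no true difference there is nothing to attenuate, and coverage stays at 0.95.

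**2. Simulated MaxDiff data.** Best-worst choices were simulated for 100 patients and 924 professionals, with a true difference of 0.7 logits on half the items, and fitted by a hierarchical Bayes multinomial logit. Mean fraction of the difference retained with a common mean and a second-step comparison:

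| Items / sets | SD 1 | SD 2 |
|---|---|---|
| 20 / 10 | 0.38 | 0.42 |
| 20 / 15 | 0.48 | 0.61 |
| 30 / 15 | 0.38 | 0.41 |
| 12 / 12 | 0.52 | 0.72 |
| 12 / 24 | not run | 0.79 |
| 40 / 12 | 0.37 | not run |

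Single runs ranged from 0.35 to 0.91. Coverage ranged from 0.35 to 1.00, mostly 0.35 to 0.85. Three runs with no true difference had coverage of 0.95 to 1.00.

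With a group term but individual posterior means still compared in a second step, the attenuation went. The second-step SE was 0.33 to 0.74 of the upper-level posterior SD (for example 0.057 against 0.173), and coverage was 0.45 to 0.92.

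With the difference read from the upper-level posterior, 0.73 to 1.18 of the truth was recovered (most runs 0.9 to 1.1), with coverage of 0.85 to 1.00 per run.

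**3. A second simulation** used 20 items, 370 professionals, 40 patients, within-group SD 1 and group-difference SD 0.8. With a common mean it retained 46% (10 sets) and 57% (15 sets), with coverage of 38% and 48%. With group in the upper level, recovery was 100% to 102% and coverage 91% to 94%.

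All runs are illustrative: few replicates and short chains.

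**The case against.** The strongest reply is that the article states neither harmful choice. Fitting each group separately, or with group as a covariate, fits the same sentence, and upper-level detail is what a condensed article leaves to a fuller plan. That stands against any flat claim that scores are shrunk to the overall mean. It does not remove the point, because the article does commit to a separate second step, and a comparison of point scores fails under either structure.

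Several stronger readings are tempting and are not supported:

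- **That differences come out about halved.** This needs a reliability near 0.5. Items, sets and heterogeneity are not given, and retention ran from 0.35 to 0.91 over the assumed settings.
- **That the tests are invalid whatever the model.** With a common mean, estimate and standard error shrink together and the test of no difference stays about valid. Only with group-specific means does the test itself become too liberal.
- **That the bias is worst for small groups such as neurosurgeons.** L contains no group size, and no simulation varied it or included neurosurgeons. Patients' scores do move further, because professionals dominate the overall mean, but that is not a greater attenuation of the difference.
- **That the top-ten list is wrong.** This was not shown. Shrinkage toward the overall mean largely preserves overall item means, and no group difference is a named outcome.

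The expert panel, which includes every profession and patient representatives, also gives some protection when the strategy is refined.

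**Conclusion.** The point holds conditionally and is worth acting on. If individual point scores are compared in SPSS, the reported group differences will have intervals that are too narrow under either upper-level structure.

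- **One common mean:** the differences are also attenuated by the score reliability, illustratively to between 35% and 91% of their true size. The test of no difference remains about right.
- **Group-specific means:** the size is right, but standard errors are too small by roughly the reliability factor, so intervals and tests are both anti-conservative.

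These figures rest on assumed items, sets, heterogeneity and full response. The direction does not, because reliability below 1 is enough. The consequence is limited to the size and precision of differences between professions and patients, which inform tailoring. The single top-ten list is not shown to be affected. This is a change that should be made, not a flaw that undermines the phase.

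**What to change.** Replace the second step in the phase A(ii) Analysis section. State that respondent group, with six levels (GPs, physical therapists, neurologists, neurosurgeons, orthopedic surgeons, patients), enters the upper level of the hierarchical Bayes model. State that group means, group differences and 95% intervals are taken directly from the posterior draws, and that individual point scores are not exported for group comparison in SPSS. If a group term is already planned, say so; the SPSS comparison should still be replaced. Each item's posterior probability of being in the top ten could be reported from the same draws, but that is optional.

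The cost is a wording change and a little more analysis work, with no new data or respondents. Intervals will be wider than those from the SPSS step, because they carry the uncertainty in the scores.
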